## Aims and objectives

The main purpose of the trial is to establish whether Thumos increases resilience and improves mental health in medical students.

The primary objective is:

To determine whether Thumos is superior to the control condition (services as usual; SAU) at 4-month follow-up in increasing psychological resilience in medical students.

Secondary objectives are:

1. To determine whether Thumos is superior to SAU at 9-month follow-up in increasing psychological resilience.2. To determine whether Thumos is superior to SAU at 4-month and 9-month follow-ups in the endpoints of confidence, burnout, depression, mental health, and self-reported sickness absence.3. To assess acceptability and how Thumos is delivered in practice through a process evaluation with users, medical educators, and providers

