## Materials and Methods

### Trial design

This study is a randomised controlled parallel groups intervention trial (see S1 CONSORT Checklist in S1 File). All United Kingdom (UK) medical schools will be invited to participate (see S3 Appendix 1 in S3 File). Participants will be self-selecting and screened for eligibility based on the criteria that they are a) UK medical student and b) in a year of study that contains a placement of one week or longer. The trial will compare Thumos to a control condition of services as usual (SAU), where medical students in either condition can continue to access available mental health support as they usually would. Data collection will occur at four time-points, Time 1 (T1), pre-intervention (baseline); Time 2 (T2), post-intervention (following completion of Thumos/6 weeks after baseline for control group); Time 3 (T3), 4 months following baseline and Time 4 (T4), 9 month following baseline (see Fig 1). All elements will be conducted online, with questionnaires administered via Qualtrics and interviews/intervention sessions via online video platform. Participants will be contacted to complete the post-baseline measures via Qualtrics using email as the first point of contact and subsequent attempts to contact will be via SMS or email. All participants that complete post-baseline measures will be awarded a £10 shopping voucher per survey as compensation. Informed consent will also be taken online, with participants asked to read the information sheet and provide written informed consent via Qualtrics prior to responding to any data collection items (see S4 Appendix 2 in S4 File). A process evaluation will include medical student participants, medical educators from medical schools of participating students and the Thumos therapists.

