### Sample size calculation

Simulations (using *powerlmm*) gave approximately 80% power with 200 participants to detect *d* = 0.50 in BRS at four months (T3; two-sided α = .05). They included repeated measurements, participant intraclass correlations of 0.30-0.50 and dropout by T4 of 30% in Thumos and 40% in services-as-usual. Adding 10% for uncertainty in these assumptions yielded a final target of N = 220 participants randomised 1:1 to Thumos or services‑as‑usual.

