### Statistical Analysis

Analyses will use R and follow the statistical analysis plan (SAP; S2 File). Participants will be analysed as randomised, whatever intervention they receive. Those without follow-up outcomes will appear in flow and baseline summaries but not the primary outcome model. Treatment labels will remain masked until the primary dataset is locked and masked primary results are checked.

Recruitment, retention and adherence will be summarised as counts and percentages. Minimum adherence requires both workshops within six weeks of randomisation, with at least 75% attendance at each; the individual call is not required.

Baseline characteristics will be summarised by arm using means and standard deviations, medians and interquartile ranges, or counts and percentages, as appropriate. Absolute standardised differences above 0.20 will be highlighted, without significance testing or changes to prespecified adjustment covariates.

The primary outcome is BRS at four months (T3). A repeated measures linear mixed model will include BRS at T2–T4, with fixed effects for arm, categorical time, their interaction, baseline BRS, age, gender and medical school. We will use restricted maximum likelihood estimation and Kenward–Roger tests and confidence intervals. Within-participant covariance will be unstructured, or first-order autoregressive if the model fails to converge. The primary comparison is the adjusted T3 mean difference, Thumos minus services as usual, tested two-sided at α = .05. We will report adjusted arm means, mean differences and Cohen’s *d (using the pooled baseline standard deviation),* with 95% confidence intervals.

Continuous secondary outcomes will use the same approach, adjusted for each outcome’s baseline value. The two sickness absence counts will use separate Poisson mixed models with a log link and participant random intercept, or negative binomial models if overdispersed. We will report adjusted incidence rate ratios, marginal mean days lost by arm and absolute differences, with 95% confidence intervals. QALYs from baseline to T4 will be calculated as the area under the ReQoL-UI utility curve using linear interpolation. They will be compared using linear regression adjusted for baseline utility, age, gender and medical school, within multiple imputation.

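### If the unstructured model fails, the only stated fallback is first-order autoregressive, which usually assumes one variance at all visits; a fallback with visit-specific variances would protect the T4 intervals at almost no cost (minor)

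*Protocol article*

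**What the plan says.** All references are to the protocol article.

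- **Model.** Under Statistical Analysis: "A repeated measures linear mixed model will include BRS at T2–T4". Baseline BRS enters as a single covariate, and no baseline-by-time interaction is listed.
- **Covariance.** "Within-participant covariance will be unstructured, or first-order autoregressive if the model fails to converge". No form with visit-specific variances is named.
- **Inference.** "We will use restricted maximum likelihood estimation and Kenward–Roger tests and confidence intervals".
- **Primary test.** "The primary comparison is the adjusted T3 mean difference, Thumos minus services as usual, tested two-sided at α = .05".
- **Visit times.** Under Trial design, T2 follows completion of Thumos, or is "6 weeks after baseline for control group"; then "Time 3 (T3), 4 months following baseline and Time 4 (T4), 9 month following baseline".
- **Reach.** Continuous secondary outcomes follow the same approach. At T4 these are BRS, the confidence score, the burnout total and its two subscales, PHQ-9 and the ReQoL-UI utility. BRS at T4 answers the first secondary objective: "To determine whether Thumos is superior to SAU at 9-month follow-up in increasing psychological resilience". Sickness absence and QALYs have other models and are not concerned.
- **Related safeguard.** Severe problems of non-normality or unequal residual variance lead to a sensitivity analysis with participant-clustered robust standard errors. Robustness is then judged on whether the direction and size of the T3 effect hold up.
- **Status of T4.** Secondary findings are called supportive, with false discovery rate adjustment within a T4 family.

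**The concern.** Standard AR(1) has two parameters, one variance and one correlation, where the unstructured form at three visits has six. The common variance is a weighted average over visits. A visit whose true residual variance lies above that average gets a standard error that is too small, and a visit below it gets one that is too large. Kenward–Roger allows for uncertainty in the estimated covariance parameters. It does not repair a wrong covariance structure.

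T4 is the visit most exposed. If baseline predicts BRS less well at nine months than at six weeks, the residual variance is largest at T4. T4 also has the fewest responders, so it weighs least in the average. At stake are the T4 intervals and the p-values that enter the T4 false discovery rate family.

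**Working it through.** **1. The plan's own figure.** The sample size section "gave approximately 80% power with 200 participants to detect" d = 0.50, with 30% and 40% dropout by T4. As a closed-form approximation, 100 per arm leaves 70 and 60. The standard error in SD units is √(1/60 + 1/70) = 0.176, and 0.50/0.176 − 1.96 = 0.88, so power is 81.1%. Then 200 × 1.10 = 220. The figure reproduces and does not depend on the fallback.

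**2. Visit gaps.** Four months is 17.4 weeks and nine months is 39.1 weeks. The gaps are therefore 17.4 − 6 = 11.4 and 39.1 − 17.4 = 21.7 weeks.

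**3. Why the variances may differ.** Assume equal marginal SDs of 1 and a single baseline slope b. The residual variance at visit t is 1 + b² − 2b·r_t, where r_t is the correlation with baseline. With complete data the AR(1) variance is close to the simple mean of the three, so

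SE ratio at T4 (model / true) ≈ √(mean variance / T4 variance), and type I error = 2[1 − Φ(1.96 × ratio)].

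The article gives no r_t, so the values below are assumptions, with b = 0.5:

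| r at T2/T3/T4 | Residual variances | Mean | T4 ratio | T4 type I error | T3 type I error |
|---|---|---|---|---|---|
| 0.50/0.50/0.50 | 0.75, 0.75, 0.75 | 0.750 | 1.00 | 5.0% | 5.0% |
| 0.55/0.50/0.45 | 0.70, 0.75, 0.80 | 0.750 | 0.97 | 5.8% | 5.0% |
| 0.65/0.50/0.40 | 0.60, 0.75, 0.85 | 0.733 | 0.93 | 6.9% | 5.3% |
| 0.75/0.50/0.30 | 0.50, 0.75, 0.95 | 0.733 | 0.88 | 8.5% | 5.3% |

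**4. With dropout.** A large-sample calculation compared the best-fitting AR(1) model SE with the sandwich SE, at 110 per arm. T4 dropout was as in the article and earlier retention was assumed. For the three fading rows it gave T4 ratios of 0.96–0.97, 0.92 and 0.86, or type I error of about 6%, 7% and 9%. T3 error was 5.0–5.9%.

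**5. By simulation under no effect.** N = 220, dropout depending on the previous value, 3,000 trials per setting, for the same three fading rows:

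| Fallback | T4 empirical SE / model SE | T4 type I error | T3 type I error |
|---|---|---|---|
| AR(1) | 0.1515/0.1446, 0.1567/0.1414, 0.1660/0.1401 | 6.4%, 8.0%, 9.5% | 5.3–6.0% |
| Heterogeneous AR(1) | 0.1516/0.1503, 0.1574/0.1559, 0.1696/0.1674 | 5.6%, 5.7%, 5.5% | 4.8–5.5% |

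The AR(1) model SE is 5%, 10% and 16% too small (for example 0.1414/0.1567 = 0.90). A second, separate simulation of the two stronger settings gave 6.4–8.2% under AR(1) and 4.4–4.6% under heterogeneous AR(1). The unstructured fit converged in all 2,000 of its trials.

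**6. Either direction.** Setting residual SDs directly (assumed), with and without the stated dropout:

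| SD at T2/T3/T4 | T4 SE ratio | T4 coverage of 95% interval |
|---|---|---|
| 0.8/1.0/1.2 | 0.82–0.85 | 89.2–90.3% |
| 0.9/1.0/1.1 | 0.89–0.91 | 92.0–92.6% |
| equal | 0.988–1.013 | 94.7–95.3% |
| 1.1/1.0/0.9 | 1.11–1.15 | 97.1–97.6% |
| 1.2/1.0/0.8 | 1.27–1.32 | 98.7–99.0% |

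The equal-SD row includes correlations that decay over 6, 17 and 39 weeks. Spacing alone therefore moves the T4 SE by about 1% at most. Patterns in which T3 itself has the highest or lowest variance moved T3 coverage to between 91% and 98%.

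**The case against.** The case against is strong on several counts.

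- **No visit SDs or between-visit correlations are given.** The only correlation in the article is an intraclass correlation of 0.30–0.50. Read as constant over time, it gives a T4 ratio of 1.00 and coverage of 95.0–95.1%. This stands: every figure above 5% rests on an assumed pattern, and a fall from 0.75 to 0.30 is an extreme one.
- **The trigger is rare and the target is not confirmatory.** Unstructured covariance is the main model, with six parameters and a planned 220 participants. This stands and sets the severity.
- **A safeguard exists.** The robust standard errors do address unequal variances, but only as a sensitivity analysis when the problem is severe. The main interval and the p-values in the T4 family stay as they are. Changing standard errors does not move the estimate, so a criterion based on the direction and size of the T3 effect cannot flag an interval that is too narrow. It also does not look at T4.
- **The statistical analysis plan is not shown.** The article's term does not exclude heterogeneous variances. If the full plan specifies them, the point falls away; the article's wording, read in the usual sense, does not.

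A reader might infer that T4 intervals are too narrow whenever the fallback is used, or that the uneven spacing is the main fault. Neither follows. The direction depends on variances that the article does not report, and spacing contributes almost nothing.

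**Conclusion.** The point holds in a limited form and is minor. If the unstructured fit fails and AR(1) is fitted with one variance, standard errors may be wrong in either direction when residual variances differ by visit. With correlation to baseline that fades over time, T4 type I error is about 6 to 9% (9.5% in the most extreme simulated setting) and T3 stays between 5% and 6%. With constant correlation and equal variances there is no error. With lower variance at T4 the intervals are too wide. These sizes rest on assumed correlations and SDs, assumed retention before T4, and the usual reading of first-order autoregressive. Nothing here affects the main model or the stated power.

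**What to change.** Prespecify an order of fallbacks, before unmasking and for BRS and all continuous secondary outcomes alike:

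1. Unstructured, as now.
2. If it does not converge, heterogeneous AR(1) or heterogeneous compound symmetry (name one), with REML and Kenward–Roger kept.
3. Only if that also fails, homogeneous AR(1), with participant-clustered robust standard errors for the reported interval and p-value, not only as a sensitivity analysis.

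State in the results which structure was used for each outcome. If the statistical analysis plan already names a heterogeneous form, it is enough to say so in the article.

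The cost is a few words and two extra variance parameters (four against two for AR(1), still fewer than the six of unstructured), with no extra data. In the simulation the empirical T4 SE was practically unchanged in the mildest setting (0.1516 against 0.1515) and about 2% larger in the strongest (0.1696 against 0.1660), so the gain is correct intervals, not precision.

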### Intervention

#### Participants randomised to THUMOS (Experimental group).

Thumos is a brief, manualised cognitive-behavioural coaching programme developed specifically for medical students, involving case studies of stressful events medical students may experience on placements. It is based upon the principles of the Reboot (Recovery-boosting) coaching programme, an earlier CBT-based resilience intervention for healthcare professionals and trainees [9,22–26]. Thumos is preventative in focus, equipping students with cognitive and behavioural strategies before, rather than only in response to, the stressful events intrinsic to clinical training. It is grounded in cognitive-behavioural therapy (CBT), in which thoughts, emotions, physical sensations and behaviours are understood as interconnected, such that modifying unhelpful thinking and behaviour can improve emotional wellbeing [28,29]. It also draws on resilience theory [30]. The strategies taught are cognitive (for example, challenging negative automatic thoughts and reattributing responsibility), behavioural (for example, mood-boosting activities, problem-solving and breathing exercises) and meta-cognitive (worry postponement and gratitude). The full intervention manual is available from the authors on request.

The programme runs over four weeks and comprises two online group workshops (120 minutes each, in stable groups typically of around four to eight) and one individual coaching call (60 minutes), with an intervening practice week. All sessions are delivered remotely by qualified therapists (HCPC-registered Clinical Psychologists or BABCP-accredited CBT therapists) trained in the Thumos protocol, and participants receive a workbook in advance.

**Workshop 1** addresses the CBT model, identifying and challenging negative automatic thoughts, common unhelpful thinking habits (for example, catastrophising and mind-reading), and the role of beliefs and self-esteem. Individual exercises include mapping a personal placement stressor onto the CBT model (identifying the most distressing “hot thought”) and completing a thought record. Group-based activities include a facilitator-led formulation of a shared example and discussion of a medical-student case study to spot thinking habits.

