Support access will be described by arm and time, not treated as an outcome or covariate. Therapy group and therapist clustering will not be modelled. Secondary and exploratory findings will be supportive, not confirmatory. We will report unadjusted and Benjamini-Hochberg false discovery rate adjusted *p* values within separate T3 and T4 secondary outcome families [38], including BRS only at T4.

Mixed models will use available outcomes, assuming data are missing at random (MAR) given observed outcomes and covariates. We will summarise missingness patterns, response rates and stated reasons for non-response, and assess predictors using logistic regression.

Sensitivity analyses will include multiple imputation under MAR, pooled using Rubin’s rules; pattern mixture adjustments subtracting 0.10, 0.20 or 0.30 points from imputed T3/T4 BRS values in Thumos only; and carrying forward the latest observed value, using baseline if no follow-up value exists. Per protocol analyses will exclude major protocol deviations and non-adherent Thumos participants and require valid T3 BRS within 12–24 weeks of baseline.

A supplementary complier average causal effect analysis of T3 BRS will use a single instrumental variables model fitted by two-stage least squares, with allocation as the instrument for minimum adherence. Both stages will adjust for baseline BRS, age, gender and medical school. All randomised participants will be included, using multiple imputation for missing outcomes. We will report the effect and 95% confidence interval, Thumos adherence proportion and first-stage partial *F* statistic.

Residual and influence diagnostics will check model assumptions. Severe non-normality or unequal residual variances will prompt sensitivity analysis using robust standard errors clustered by participant. Robustness will be judged by consistency in the T3 effect’s direction and magnitude. Scale reliability will be reported as Cronbach’s alpha and McDonald’s omega with 95% bootstrap confidence intervals. Adverse and serious adverse events will be summarised by arm, with risk differences and 95% confidence intervals but no hypothesis tests.

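### Thumos is delivered in stable therapist-led groups, but the plan rules out any allowance for group or therapist clustering; if outcomes are positively correlated within groups, the T3 interval is too narrow

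*Protocol article*

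**What the plan says.** All references are to the protocol article.

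- **Delivery.** The section on participants randomised to Thumos describes two 120-minute online workshops, "in stable groups typically of around four to eight", and one individual call, all led by qualified therapists. The number of therapists is not given. The control-group section says that controls receive no alternative intervention.
- **Primary analysis.** Under Statistical Analysis, the BRS model has fixed effects and a within-participant covariance. "The primary comparison is the adjusted T3 mean difference, Thumos minus services as usual, tested two-sided at α = .05".
- **Clustering.** The same section states: "Therapy group and therapist clustering will not be modelled". No reason is given.
- **Sensitivity analyses.** Those listed deal with missing data, adherence and model diagnostics. The only robust-variance option applies if diagnostics are poor, and it uses "robust standard errors clustered by participant".
- **Sample size.** The simulations gave "approximately 80% power with 200 participants to detect *d* = 0.50 in BRS at four months", with "participant intraclass correlations of 0.30-0.50 and dropout by T4 of 30% in Thumos and 40% in services-as-usual". The ICC there describes repeated measures on one participant. No therapy-group or therapist ICC is listed.

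**The concern.** Members of a Thumos group share four hours of workshops, joint case work and a therapist. Anything that makes one group go better than another (its chemistry, the therapist's skill, a disruptive session) moves the outcomes of all its members together. Controls have no such structure. A model that treats every Thumos participant as independent then takes the Thumos mean to be more precise than it is.

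Baseline BRS and medical school are in the model and may absorb similarity that members bring with them. They cannot absorb similarity created by the sessions. Robust standard errors clustered by participant do not help either, because the correlation lies between participants.

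At stake are the coverage of the primary interval and the reading of a borderline result. The trial is presented as a definitive test of effectiveness. As planned, its analysis could not show whether a marginal benefit came from a few groups or one therapist. The continuous secondary outcomes use the same approach, although they are declared supportive only.

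**Working it through.** **1. The plan's own power figure.** 200 randomised 1:1, less 30% and 40% dropout, leaves 70 vs 60. A two-sample normal formula for d = 0.50 at two-sided 0.05 gives 81.1% (80.5% with the noncentral t). This matches the stated figure of about 80%, with no group clustering included. The uplift is 200 × 1.10 = 220, the stated "final target of N = 220 participants randomised 1:1". The planned simulations themselves cannot be rerun from the article.

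**2. Inputs for the clustering check.**
- From the documents: 110 per arm; groups of 4 to 8, so about 110/8 ≈ 14 to 110/4 ≈ 28 groups; dropout by T4 of 30% and 40%.
- Assumed: a group ICC (ρ) of 0.01 to 0.10.
- Two attrition cases bracket T3. The first applies full T4 dropout: n₁ = 77, n₂ = 66, and the mean observed group size m is 70% of the group size at the start. The second assumes no dropout: 110 vs 110.

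**3. Formulae.** Only the Thumos mean is inflated, by 1 + (m − 1)ρ. The ratio k of correct to reported standard error satisfies

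k² = 1 + (m − 1)ρ × n₂/(n₁ + n₂)

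and the actual two-sided error is 2[1 − Φ(1.96/k)].

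**4. Worked examples.**
- Groups of 4, ρ = 0.05, with dropout: m = 2.8, so k² = 1 + 1.8 × 0.05 × 66/143 = 1.042, k = 1.021, error 5.5%.
- Groups of 8, ρ = 0.10, no dropout: k² = 1 + 7 × 0.10 × 0.5 = 1.35, k = 1.162, error 9.2%.

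| Group size | ICC | k and error, 77 vs 66 | k and error, 110 vs 110 |
|---|---|---|---|
| 4 | 0.01 | 1.004, 5.1% | 1.007, 5.2% |
| 8 | 0.02 | 1.021, 5.5% | 1.034, 5.8% |
| 4 | 0.05 | 1.021, 5.5% | 1.037, 5.9% |
| 6 | 0.05 | 1.036, 5.9% | 1.061, 6.5% |
| 8 | 0.05 | 1.052, 6.2% | 1.084, 7.1% |
| 4 | 0.10 | 1.041, 6.0% | 1.072, 6.8% |
| 6 | 0.10 | 1.071, 6.7% | 1.118, 8.0% |
| 8 | 0.10 | 1.101, 7.5% | 1.162, 9.2% |

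The correct standard error is thus about 2% to 8% larger than the reported one at ICC 0.05, and 4% to 16% larger at ICC 0.10.

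**5. Simulation check.** Using 40,000 null trials per setting, an unclustered t-test and the planned dropout, the error for groups of 4, 6 and 8 was 5.6%, 5.8% and 6.4% at ICC 0.05, and 6.0%, 6.7% and 7.7% at ICC 0.10. At ICC 0 it was 4.9% to 5.1%.

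**6. Therapists.** Assume 4 therapists with a therapist ICC of 0.02, added to group ICC 0.05 in groups of 6, with 77 vs 66. The inflation of the Thumos variance rises from 1.16 to 1.16 + (77/4 − 1) × 0.02 ≈ 1.52, and the error from 5.9% to 7.9%. The number of therapists and both ICCs are assumptions.

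**7. Power at N = 220 (77 vs 66), d = 0.50.** Unclustered, it is 84.6%. With clustering allowed for:

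| Group size | ICC 0.05 | ICC 0.10 |
|---|---|---|
| 4 | 83.2% | 81.7% |
| 6 | 82.0% | 79.5% |
| 8 | 80.9% | 77.3% |

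**The case against.** **The ICC is unknown.** A reader might infer that the interval is certainly too narrow and the 5% level certainly broken. The documents do not support this. They give no group ICC. At 0.01 to 0.02 the excess is under one percentage point, and at zero there is none. This objection stands, so the point must be stated conditionally. It does not justify fixing the ICC at zero without estimating it.

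**Allocation is by individual.** If Thumos changed nobody's outcome, sorting its participants into groups after randomisation would alter nothing, and the unclustered test would keep its level. The error inflation above concerns a zero average effect with real differences between groups or therapists. This is correct and narrows the type I error argument. The interval still under-covers the effect expected across such groups and therapists whenever delivery makes outcomes vary between them.

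**Power.** A reader might also infer that the sample size is inadequate. With the uplift to 220, power stays near or above 80% in most settings examined. What remains is that the stated assumptions do not mention clustering.

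**Masking.** Randomisation and Blinding and Statistical Analysis both require masked primary results to be checked first. A group term in one arm would reveal which label is Thumos. This stands and determines the order of the analyses in the fix.

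**Unseen documents.** The reason for the choice may be in the full protocol or SAP. It may be, but the exclusion is an explicit rule in the article and not a detail left open.

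**Conclusion.** The point holds in conditional form. The plan expressly excludes an allowance for group and therapist clustering in a partially nested design, and nothing else in the listed analyses supplies one. For any positive correlation arising from the shared sessions or therapist, the T3 interval is too narrow.

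Under assumed group ICCs up to 0.10, the excess over the nominal 5% ranges from negligible to about four percentage points. Shared therapists would add to it. The upper end needs groups of eight, an ICC of 0.10 and no dropout. With the planned T4 dropout the highest figure is 7.5%. The estimate of the treatment difference is not what is challenged here; its stated precision is.

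**What to change.** 1. **Replace the sentence that excludes clustering** with a prespecified partially nested linear mixed model for T3 BRS and the continuous secondary outcomes. It has a random intercept for therapy group in the Thumos arm only. Control participants, and Thumos participants never placed in a group, are singletons. Use Kenward–Roger degrees of freedom, and report the group ICC with its confidence interval.
2. **Therapist:** add as a further sensitivity analysis if the number of therapists allows.
3. **Keep the masking.** Run and check the planned unclustered model under masked labels. Then run the partially nested script, locked beforehand, immediately after unmasking. Base the T3 conclusion on the clustered interval. At minimum, report it beside the primary result as a required sensitivity analysis.
4. **Count and QALY models:** use standard errors clustered by therapy group, with each control participant as its own cluster. Kenward–Roger is a linear mixed model method. It does not carry over to the Poisson or negative binomial models, and the QALY regression is not a mixed model. Cluster the fallback robust standard errors in the same way.
5. **Sample size section:** state that the listed power assumptions include no therapy-group ICC.

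The cost is a slightly wider interval and a small amount of extra analysis. Design, recruitment and questionnaires do not change. Group membership must be carried into the analysis file.

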Multiple risk factors unique to medical training have been implicated in these mental health difficulties, notably demanding academic requirements and perfectionism-related cognitive patterns [15,16] and exposure to stressful clinical events on placement [17]. Indeed, rates of burnout in medical students increase significantly during the years involving clinical placements [18]. However, there has been a lack of interventions tailored for medical students and none which prepare medical students for stressful workplace events [19]. Previous evaluations of mental health support for medical students have predominantly examined non-tailored approaches such as mindfulness-based programmes, relaxation techniques, and yoga [19]. Evidence for these interventions is weak and mixed, and they have been criticised for lacking relevance [20]. A recent meta-analysis of resilience interventions for medical students indicated that these interventions are moderately effective at reducing stress and mildly effective at increasing resilience within medical students [21]. The implication that these interventions may have more favourable impacts on stress suggests that further research is required to examine the specific factors that influence resilience. There is an urgent need for effective, preventative interventions which help students cope with the specific occupational stressors they will encounter during their placements, training, and beyond.

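### Carrying the last or baseline score forward should not count when the robustness of the four-month BRS effect is judged

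*Protocol article*

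**What the plan says.** All of this is in the Statistical Analysis section of the protocol article unless stated otherwise.

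- **Primary analysis.** A repeated measures mixed model of BRS at T2 to T4. "The primary comparison is the adjusted T3 mean difference, Thumos minus services as usual, tested two-sided at α = .05". On missing data: "Mixed models will use available outcomes, assuming data are missing at random (MAR) given observed outcomes and covariates".
- **Sensitivity analyses for missing data.** Two of the three are "multiple imputation under MAR, pooled using Rubin’s rules; pattern mixture adjustments subtracting 0.10, 0.20 or 0.30 points", the subtraction applying to imputed T3 and T4 values in Thumos only. The third is "carrying forward the latest observed value, using baseline if no follow-up value exists".
- **Criterion.** "Robustness will be judged by consistency in the T3 effect’s direction and magnitude".
- **Dropout.** The Sample size calculation section assumes 30% loss in Thumos and 40% in services as usual (SAU) by T4, the nine-month visit. It gives no figure for T3.

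The article gives no reason for the carry-forward analysis and does not say in which direction it is expected to err.

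**The concern.** A sensitivity analysis is useful when it changes one stated assumption and the reader knows what that change does. The delta adjustments meet this test. Carry-forward does not, for three reasons.

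1. It holds each missing score at its last value. A participant missing at T3 keeps the T2 score if there is one, and otherwise the baseline score. The first rule removes any change between T2 and T3, and the second imposes no change at all. The two can err in opposite directions, and the mix depends on who is lost and when.
2. Planned dropout differs by arm, so any drift common to both arms is frozen more often in SAU.
3. The filled-in values enter as if observed, so the standard error ignores imputation uncertainty. The multiple imputation listed beside it does account for this.

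At stake is how the result is described. Agreement with the primary model could be coincidence and disagreement could be artefact, yet under the stated criterion either would count in the judgement of robustness.

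**Working it through.** **Inputs from the article:** d = 0.50 at T3; 200 participants before uplift and 220 after; participant intraclass correlation 0.30–0.50; dropout by T4 of 30% (Thumos) and 40% (SAU).

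**Assumed, because the article does not state them:** dropout by T3, the share of T3-missing participants who have a T2 score, the size of the T2 effect, and drift in SAU.

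**The plan's own figure.** The Sample size calculation section says its simulations "gave approximately 80% power with 200 participants to detect *d* = 0.50 in BRS at four months (T3; two-sided α = .05". A normal approximation with the T4 retention figures (70 and 60 of 100 per arm) gives power = Φ(0.50/√(1/70 + 1/60) − 1.96) = Φ(0.88) = 0.811. The stated power is reproduced and does not depend on the carry-forward analysis.

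**Simple bounds for each rule**

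- Baseline carried, no SAU drift: effect = 0.50 × (1 − share of Thumos with no follow-up). At 10%: 0.50 × 0.90 = 0.45. At 15%: 0.50 × 0.85 = 0.425, or 0.43.
- T2 carried: inflation = share carried × (T2 effect − T3 effect). Low: 0.10 × 0.2 = 0.02 SD. High: 0.30 × 0.3 = 0.09 SD. If the effect does not fade, the inflation is zero. If it grows, the sign reverses.

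**Both rules together, with SAU drift, under purely random dropout**

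Expected T3 difference = (1 − dT)(c3 + e3) + dT·q·(c2 + e2) − (1 − dC)·c3 − dC·q·c2

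Here dT and dC are dropout by T3 in Thumos and SAU, c2 and c3 the SAU change from baseline, e2 and e3 the treatment effects, and q the share of T3-missing participants with a T2 score. Take e3 = 0.50 and set T3 dropout at the T4 figures (0.30 and 0.40):

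- q = 0, no drift: 0.70 × 0.50 = 0.35.
- q = 0, SAU falls 0.4 SD: 0.70 × 0.10 − 0.60 × (−0.4) = 0.07 + 0.24 = 0.31.
- q = 1, no drift, e2 = 0.25: 0.35 + 0.30 × 0.25 = 0.425.
- q = 1, no drift, e2 = 0.50: 0.35 + 0.30 × 0.50 = 0.50, no bias.
- q = 1, no drift, e2 = 0.80: 0.35 + 0.30 × 0.80 = 0.59.
- q = 1, SAU rises 0.2 then 0.4 SD, e2 = 0.80: 0.70 × 0.90 + 0.30 × 1.00 − 0.60 × 0.4 − 0.40 × 0.2 = 0.61.

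Over all combinations tried (e2 of 0.25, 0.5 and 0.8; SAU change by T3 of −0.4, 0 and +0.4 SD; q of 0, 0.5 and 1) the range is 0.31 to 0.61. With half that dropout (15% and 20%) it is 0.41 to 0.56.

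**No true T3 effect**

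- Both arms fall 0.4 SD and baseline is carried: 0.70 × (−0.4) − 0.60 × (−0.4) = −0.04. If both rise 0.4 SD, the result is +0.04. Unequal dropout alone produces this.
- A T2-only effect of 0.3, with T2 carried for all missing: 0.30 × 0.3 = +0.09.

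**Precision.** Simulation with 110 per arm, correlation 0.5, T3 dropout of 30% and 40%, adjustment for baseline and 3,000 replicates per scenario gave a mean standard error of 0.10–0.12 for carry-forward, against 0.146 for an available-case analysis. With all 220 observed it would be about √(0.75 × 2/110) = 0.117, so carry-forward reports roughly the precision of complete data, or better. Coverage of its 95% intervals was 76–94%, reflecting bias and understated error together. In the T2-only scenario it rejected 11% of the time against a nominal 5%. With a true effect of 0.50 the available-case analysis returned 0.50.

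**The case against.** The strongest reply is that this is one supplementary line. The primary estimate, its test and the sample size do not depend on it, and the article already plans multiple imputation and graded, Thumos-only delta adjustments that probe unfavourable departures from missing at random. All of that stands. It limits the weight of the point and makes a further reference-based analysis optional.

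A second reply is that the robustness sentence directly follows the one on robust standard errors and may concern only those. Its wording is general, however, and robust standard errors mainly change precision, so direction and magnitude fit the missing-data analyses at least as well. The full analysis plan (S2 File) was not available and may label the analysis more narrowly.

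A third reply is that carry-forward is conservative. At a true effect of 0.50 SD that held in every random-dropout scenario where baseline was carried for all missing. The planned rule carries T2 whenever it exists, and that can overstate benefit.

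A reader might also infer more than the article supports:

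- **That constant scores contradict the trial's own premise.** The Introduction says "rates of burnout in medical students increase significantly during the years involving clinical placements". That concerns burnout, not BRS, and gives no within-person course over four months. Everyone eligible is already in a placement year.
- **That the benefit peaks at T2 and then fades.** The article gives no expected pattern from T2 to T3.
- **That inflation could reach 0.15 SD, or 30% of d = 0.50.** This is 0.30 × 0.5. It needs a T2 effect of d = 1.0, and the entire 30% Thumos loss planned by T4 to fall between T2 and T3. Nothing in the article points to either.
- **That carry-forward alone could certify a fading benefit as robust.** The other two analyses do not freeze T2 scores and would be read beside it.

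**Conclusion.** The point holds as a limited one. Carry-forward sits among the analyses by which robustness of the T3 effect may be judged, but its bias has no known direction and its standard error is too small, so its result cannot inform that judgement.

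On the narrower assumptions, baseline carry-forward takes 0.50 SD to 0.43–0.45 and T2 carry-forward adds 0.02–0.09 SD if an early benefit fades. The wider 0.31–0.61 range rests on setting T3 dropout at the T4 figures and on assumed T2 effects and SAU drift, so it shows that either sign is possible and is not a forecast. The deltas are in BRS points and the article gives no BRS standard deviation, so these figures cannot be set directly against them. The trial's main inference is not in question.

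**What to change.** Delete the carry-forward analysis. Alternatively, keep it, label it descriptive and state that it does not enter the robustness judgement. Either way, say that robustness to missing data rests on multiple imputation under missing at random and the planned delta adjustments.

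If a replacement is wanted, use jump-to-reference imputation: missing T3 and T4 values in Thumos are imputed from the SAU distribution given baseline and T2. This tests a clear assumption, that Thumos leavers keep no benefit. It should be labelled as conservative for Thumos.

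The cost is one wording change in the article and the analysis plan. The optional replacement can use the imputation set-up already planned. The Trial Status section expects the last follow-up by February 2027, and labels stay masked until the primary dataset is locked and the masked results are checked, so the change can be made and dated before unmasking.
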